### Protection of human subjects

All subject recruitment is directed by the study personnel. If contact is made through a third party (e.g., employer newsletter), all further communications occur privately. All participants are asked to sign activity-specific informed consent forms explaining the procedure, offering to answer questions, and informing them that they are free to withdraw their consent and discontinue participation in the study at any time without prejudice to their employment situations. Personal identifiers are requested for contact information and to ensure accurate record linkage across stages of data collection. They are not kept with the data files and will be destroyed at the end of the study. Data values for small cells (e.g., fewer than 5 people per facility/job group/gender) will not be reported, to protect anonymity.

## Discussion

Overall, the SHIFT study will extend the knowledge about the effectiveness of a participatory approach to Total Worker Health in the healthcare sector. The HWPP will be implemented with attention to all job groups, for the broad objectives of protecting employee safety and fostering health and well-being. It is hoped that this integrated approach will complement and strengthen existing workplace safety and health initiatives and promote organizational learning, producing synergistic effects [46]. We expect to obtain valuable information on program effectiveness for improving employee safety and health, program impact at the individual and organizational levels, facilitators and barriers to program implementation, and how the HWPP might be further improved, especially for public sector facilities.

### Methodologic considerations

Although workplace integration of programs in occupational health and health promotion seems desirable, there are challenges. One is that integrated programs require more time, effort, and commitment from the organization [67]. For example, we expect the management steering committee to provide timely constructive feedback to interventions proposed by the DT, as well as financial and organizational resources for implementing and evaluating them. The biggest barrier to front-line employee participation in a previous healthcare program was lack of release time for employees [68]. Although obtaining such commitment from the organization takes time and effort, we believe it will be worthwhile because organization culture, environment, and leadership support are closely associated with employee safety and health [32, 69].

The standardized All-Employee Survey will be valuable for tracking large trends in the study population, but if the intervention only benefits a sub-group, any effect could be diluted and difficult to observe. Further, individual health outcomes, as well as workplace culture and organizational features, may evolve gradually enough that there is not adequate time to see changes. We have included a number of proximal endpoints to alleviate this potential challenge. For example, perceived management support of safety relates to longer-term outcomes HWPP, through the multi-level communication and organizational learning that results from the IDEAS process.

Because of the high degree of participatory decision-making, specific health targets selected may vary among DTs. The facilities have generally indicated a similar set of concerns, but even if intervention topics overlap across the sites, they will not necessarily be taken up in the same sequence. This requires that we examine both generic injury/illness outcomes, as well as problem-specific outcomes. Depending on the sequence in which the same topics are addressed in each facility, the length of follow-up time for those endpoints may vary and need to be adjusted for accordingly.

The gold standard for an intervention study is the randomized clinical trial (RCT). Ideally this study would use a cluster randomized design, where groups with similar background risk (on average) are randomly assigned to the intervention or to a control group that receives standard or current services. However, the benefits of randomization to prevent confounding are not realized except with a large sample. In this case, the intervention is administered at the level of the entire facility, and resources do not permit enrollment of enough sites. In any case, it would be difficult to find enough workplaces of a similar nature. The alternative is to compare the treatment groups on baseline characteristics that might influence the outcome. Differences can then be adjusted for with stratified analysis multivariable regression. The double-blinding in RCTs also prevents the possibility of information bias. However, double-blinding is infeasible for organization-level interventions, and other study designs, such as the stepped wedge, maybe be of equal value with attention to reducing bias [70–72]. Further, RCTs have other disadvantages, such as limited capacity to assess multi-dimensional interventions – such as this one - and incompatibility with community trust, choice, and participation often needed for successful program design and evaluation. The stepped-wedge design was selected to achieve comparable study engagement, survey participation, and data quality in all sites.

### Study revisions after the start date

After the study began, one facility withdrew by order of a manager in a central agency office, for administrative reasons. We continue to support the other facility in that pair as an immediate intervention site. Data from the unpaired facility will be utilized in comparisons with the other two immediate intervention sites, to assess generalizability of results and describe program sensitivity to institutional context.

Due to administrative delays and personnel changes, the SHIFT start-up process took about 2 years, whereas the original study design had envisioned less than 1 year needed until the Design Teams began application of the IDEAS Tool. For meaningful evaluation, the coaching in the immediate intervention group should be maintained long enough to complete at least two full intervention cycles. Coaching in the lagged intervention group will then be concurrent with that in the first group. This preserves roughly 1.5 years of the core comparison between concurrent experiences in Groups A and B. In fact, this timeline corresponds closely to the typical stepped-wedge design, where interventions are added progressively to later sites but not necessarily withdrawn from the initial ones.

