**Methods:**

Six public sector, unionized healthcare facilities are enrolled, in three pairs, matched by agency. The unit of intervention is a workplace health and safety committee, adapted here to a joint labor-management “Design Team” (DT). The DT conducts root cause analyses, prioritizes problems, identifies feasible interventions in light of the constraints and needs of the specific setting, makes business-case presentations to facility leadership, and assists in evaluation.

Following a stepped-wedge (cross-over) design, one site in each pair is randomly assigned to “immediate intervention” status, receiving the full coached intervention at baseline; in the “lagged intervention” site, coaching begins about half-way through the study. Program effectiveness and cost-effectiveness outcomes are assessed at both organizational (e.g., workers’ compensation claim and absenteeism rates, perceived management support of safety) and individual levels (e.g., self-rated health, sleep quality, leisure-time exercise). Targeted pre-post analyses will also examine specific outcomes appropriate to the topics selected for intervention. Process evaluation outcomes include fidelity of the HWPP intervention, extent of individual DT member activity, expansion of committee scope to include employee well-being, program obstacles and opportunities in each setting, and sustainability (within the available time frame).

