#### Effectiveness evaluation

The pre/post “mini-surveys” will be analyzed to assess short-term effectiveness of locally-designed interventions within the proportion of the workforce expected to benefit. Employee participation in DT-promoted activities will be compared between study groups and over time (pre- vs post-intervention).

Organizational-level improvements in worker engagement, communication or shared understanding between management and workforce, SC authorization of resources, or uptake and institutionalization of new practices will be interpreted as effectiveness of the participatory intervention process, at the overall study level.

Assuming that both groups intervene on similar topics over time, pooled effectiveness analyses will compare AES data in the immediate intervention and lagged intervention groups. If sufficient numbers of workers complete more than two surveys, we will also use a difference-in-difference approach. Reporting of individual-level outcomes (e.g., changes in occupational exposures, health beliefs and behaviors) will follow the CONSORT guidelines for cluster randomized trials [64].

Statistical power calculations for intention-to-treat comparisons of several key outcomes (Table 2) were conducted for difference-in-difference analysis, with two-sample differences at the population level. The facilities within each pair are of different workforce sizes, so we assumed conservatively the smaller of the facilities from each pair in both groups. Full-time equivalent denominators were assumed to represent 90% of headcount; a 75% response rate gave samples of about 1650 workers per group. We used a binomial distribution for proportions (e.g., smoking) and Gaussian distribution for means (e.g., body mass index (BMI)). Starting values were taken as those found in our prior healthcare study using a similar instrument [31, 32, 65]. Modest differences should be readily detectable, assuming facility-wide implementation of each HWPP intervention.

**Table 2 Tab2:** Smallest detectable differences in selected outcomes with 80% power (alpha = 0.05, two-sided *p*-value)

Outcome	Baseline value	Detectable difference
Injury rate	0.71 / FTE	.062 / FTE
Smoking	Prevalence 25.6%	6.0%
BMI	Z = 28, SD = 9	0.9
Health self-efficacy	Z = 27, SD = 8.5	0.8
Work ability	Z = 8.9, SD = 2	0.19

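### Table 2 and the 1650 workers per group were not restated after one facility withdrew, and the unpaired site's place in the immediate-versus-lagged comparison is not stated

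*Protocol article*

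**What the plan says.** The abstract describes the design: "Six public sector, unionized healthcare facilities are enrolled, in three pairs, matched by agency". Each pair has one immediate and one lagged facility, so three sites per group.

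The power paragraph (Data analysis, Effectiveness evaluation) labels the comparisons intention-to-treat and says that the calculations "were conducted for difference-in-difference analysis, with two-sample differences at the population level". The two facilities of a pair differ in workforce size, "so we assumed conservatively the smaller of the facilities from each pair in both groups". It continues: "Full-time equivalent denominators were assumed to represent 90% of headcount"; "a 75% response rate gave samples of about 1650 workers per group". Table 2 then lists detectable differences at 80% power and two-sided alpha 0.05. The paragraph concludes that modest differences should be easy to detect.

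The Discussion section Study revisions after the start date reports that one facility withdrew for administrative reasons and that its partner continues as an immediate site. On the partner's data it says: "Data from the unpaired facility will be utilized in comparisons with the other two immediate intervention sites". The stated purpose is generalizability and sensitivity to institutional context. The section keeps a comparison of Groups A and B over about 1.5 years. It does not redefine who belongs to each group, and it does not return to the sample size or Table 2.

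**The concern.** The article states a power figure and, later, an event that removes part of its basis, and it does not connect the two. A reader who takes Table 2 at face value will think the five-facility study has 80% power for those differences. On the plan's own method of calculation the lagged group has lost one of its three contributing facilities.

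The size of the loss depends on something the article leaves open. If the unpaired immediate site stays in the group comparison, three sites face two and only the lagged group shrinks. If it does not, two face two and both groups shrink. With so few facilities the choice affects both precision and whether the intention-to-treat label is accurate, so it should be fixed before the outcome data are compared.

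**Working it through.** **Inputs.** From the Effectiveness evaluation section and Table 2: n = 1650 per group, 80% power, two-sided alpha 0.05; BMI SD 9, difference 0.9; health self-efficacy SD 8.5, difference 0.8; work ability SD 2, difference 0.19; smoking 25.6%, difference 6.0%; injury rate 0.71/FTE, difference 0.062/FTE.

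**Step 1: reproduce Table 2 at 1650 per group.** For means, the detectable difference is (1.960 + 0.842) × SD × √(2/n), with √(2/1650) = 0.0348.

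- BMI: 2.802 × 9 × 0.0348 = 0.88 (stated 0.9)
- Self-efficacy: 2.802 × 8.5 × 0.0348 = 0.83 (stated 0.8)
- Work ability: 2.802 × 2 × 0.0348 = 0.195 (stated 0.19)

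For smoking and injury the stated values match a four-cell difference-in-difference variance, 2.802 × √(4p(1−p)/n):

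- Smoking: 2.802 × √(4 × 0.256 × 0.744/1650) = 0.0602 (stated 6.0%)
- Injury, binomial variance: 2.802 × √(4 × 0.71 × 0.29/1650) = 0.0626 (stated 0.062)

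Table 2 is therefore consistent with about 1650 in each group. These formulas contain no clustering term. The 1650 itself cannot be rebuilt, because no facility headcounts are given.

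**Step 2: remove the lost facility.** Assumption: each pair supplied one third of the 1650, that is 550. The lagged group becomes 1100. Power for a stated difference d is Φ(d/SE − 1.960), with SE = SD × √(1/n₁ + 1/n₂).

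*Unpaired site kept, 1650 v 1100.* √(1/1650 + 1/1100) = 0.0389.

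- BMI: SE 0.350, 0.9/0.350 = 2.57, power 73%
- Self-efficacy: SE 0.331, 0.8/0.331 = 2.42, power 68%
- Work ability: SE 0.0779, 0.19/0.0779 = 2.44, power 68%

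Detectable differences grow by √((1 + 1.5)/2) = 1.118: BMI 0.98, self-efficacy 0.93, work ability 0.22, smoking 6.02 × 1.118 = 6.7%.

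*Two complete pairs, 1100 v 1100.* √(2/1100) = 0.0426.

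- BMI: SE 0.384, 0.9/0.384 = 2.35, power 65%
- Self-efficacy: SE 0.362, 0.8/0.362 = 2.21, power 60%
- Work ability: SE 0.0853, 0.19/0.0853 = 2.23, power 61%

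Detectable differences grow by √(1650/1100) = 1.22: BMI 1.08, self-efficacy 1.02, work ability 0.24, smoking 7.4%, injury 0.077/FTE.

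**Step 3: range for the assumed share.** Power for the stated differences (lowest and highest of the three mean outcomes):

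| Lost pair's share of 1650 | Lagged n | Unpaired site kept | Two complete pairs |
|---|---|---|---|
| 20% | 1320 | 72–77% | 68–73% |
| 33% | 1100 | 68–73% | 60–65% |
| 50% | 825 | 60–65% | 48–53% |

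At full size the same formula gives 82%, 77% and 78% for the rounded differences in Table 2, so these are the values to compare against.

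**The case against.** **The exclusion is not in the text.** A reader might infer that the unpaired site is used only within the immediate group, that its before-after data are discarded, and that the controlled comparison is now two against two. The documents do not support that. The revision section names one use and rules out none. It keeps the facility as an immediate site, and the pooled survey analysis is defined by group, not by pair. What stands is narrower: the article does not say whether the site enters the group comparison.

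**A realised shortfall cannot be shown.** Site sizes are absent, and the 1650 used the smaller facility of each pair for both groups. Larger remaining sites could make up part of the loss in respondents. That is correct, so the claim is about the stated basis and not about the numbers that will be achieved. Extra respondents at the remaining sites would still not restore the third lagged facility.

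**The withdrawal did not create the few-sites problem.** A reader might say that it removed the chance of a 0.05-level test. But with three intact pairs the smallest two-sided p-value of a paired randomisation test is already 2/2³ = 0.25; with two pairs it is 2/2² = 0.50. The Methodologic considerations section itself concedes that not enough sites could be enrolled.

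**Reach is limited.** The registered process primaries are attendance, engagement, committee activity and scope of issues, none of which is in Table 2. The pooled survey analysis is also conditional on both groups taking up similar topics. This limits the consequences but does not correct the figure.

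**Three against two has its own weakness.** Sites are matched by agency, and the unpaired site's agency no longer has a concurrent control. This is a fair reason to show the two-pair analysis as well.

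**Conclusion.** The point holds in this form: the article still presents group sizes and detectable differences for three facilities per group after reporting that only five facilities remain, so the 80% power is not supported on its own basis. With equal pairs and no clustering, power for the three stated mean differences is about 68 to 73% if the unpaired site is kept and about 60 to 65% with two complete pairs. Detectable differences are larger by about 12% and 22% respectively.

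The result rests on three assumptions. The first is that the 1650 covers three pairs, which is the natural reading although the power paragraph does not repeat the number. The second is the share of the lost pair, for which the range is shown above. The third is that clustering is ignored, as the formulas that reproduce Table 2 do; allowing for it would lower all these power values and is a separate matter.

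The silence on the unpaired site is an ambiguity to resolve, not evidence that the site was dropped. This should be corrected, but it does not invalidate the study.

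**What to change.** 1. Restate the workers per group and Table 2 for the five remaining facilities, using actual site sizes, and label the present figures as those of the six-facility design.
2. In the revision section, state that the unpaired immediate site stays in the immediate-versus-lagged comparison as randomised, in addition to its use beside the other two immediate sites. Report the analysis of the two complete pairs as well.
3. Say whether that pair had been randomised before the withdrawal. The article does not give the timing, and the as-randomised label depends on it.

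The cost is a recalculation and a few sentences; no data collection changes. The downsides are slightly less favourable stated figures and, for the three-against-two comparison, reliance on the other agencies' lagged sites for a concurrent control. The two-pair analysis is there to show how much that matters.

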### Potential impact

This study of healthcare workers is innovative in not being limited to clinical personnel. There are numerous health and safety challenges for workers in other healthcare jobs, especially those of lower socioeconomic status, such as laundry, food service, housekeeping and maintenance [18].

This work will benefit both workers and employers. Rooted in participatory action research with organization support, the HWPP will ideally be sustained after the researchers step back, because employees will benefit from an improved work environment as well as safety and health through interventions proposed and implemented on their willingness. Employer support might be motivated by positive effects such as improved worker morale and engagement and lower rates of compensation claims, missed workdays, and job turnover.

## Data Availability

Data collection forms are available from the research team at: [contact]. Data files are not publicly available due to privacy guarantees to study participants, many of whom could be identified from their roles and demographic characteristics even in de-identified data sets.

## Abbreviations

AES: All-Employee Survey
CPH-NEW: Center for the Promotion of Health in the New England Workplace
DT: Design Team
HWPP: Healthy Workplace Participatory Program
IDEAS: Intervention Design and Analysis Scorecard
LPN: Licensed practical nurse
MSD: Musculoskeletal disorder
OSHA: Occupational Safety and Health Administration
RN: Registered nurse
SC: Steering Committee
SHIFT: Safety and Health through Integrated, Facilitated Teams
TWH: Total Worker Health
WC: Workers’ compensation
